## Abstract

**Background:**

Type 2 Diabetes Mellitus is one of the most disabling chronic conditions worldwide, resulting in significant human, social and economic costs and placing huge demands on health care systems. The Inala Chronic Disease Management Service aims to improve the efficiency and effectiveness of care for patients with type 2 diabetes who have been referred by their general practitioner to a specialist diabetes outpatient clinic. Care is provided by a multidisciplinary, integrated team consisting of an endocrinologist, diabetes nurse educators, General Practitioner Clinical Fellows (general practitioners who have undertaken focussed post-graduate training in complex diabetes care), and allied health personnel (a dietitian, podiatrist and psychologist).

**Methods/Design:**

Using a geographical control, this evaluation study tests the impact of this model of diabetes care provided by the service on patient outcomes compared to usual care provided at the specialist diabetes outpatient clinic. Data collection at baseline, 6 and 12-months will compare the primary outcome (glycaemic control) and secondary outcomes (serum lipid profile, blood pressure, physical activity, smoking status, quality of life, diabetes self-efficacy and cost-effectiveness).

**Discussion:**

This model of diabetes care combines the patient focus and holistic care valued by the primary care sector with the specialised knowledge and skills of hospital diabetes care. Our study will provide empirical evidence about the clinical effectiveness of this model of care.

**Trial registration:**

Australian New Zealand Clinical Trials Registry ACTRN12608000010392.

## Background

Type 2 Diabetes Mellitus (T2DM) is one of the most disabling chronic conditions worldwide, resulting in significant human, social and economic costs and placing huge demands on health care systems[1]. It affects more than 880,000 Australians 25 years or older[2], and the prevalence is increasing as more people develop the condition, the detection of the condition improves, and people with the condition live longer[3]. People with T2DM are at risk of acute and chronic micro- and macro-vascular complications including retinopathy, nephropathy, neuropathy, peripheral vascular disease, coronary heart disease and stroke; as well as mental health problems associated with living with a chronic disease. The United Kingdom Prospective Diabetes Study has demonstrated that rigorous glycaemic control can significantly reduce diabetic complications[4], underscoring the need for, and benefits of, early diagnosis and appropriate management.

In Australia, most people with T2DM receive the majority of their diabetes care from their general practitioner (GP)[5]. In 2006/07, it was the second most frequently managed chronic problem in Australian general practice, and was the reason for 3.7% of general practice encounters; a 42% increase from 1998/99[6]. Around 5% of consultations for diabetes lead to a referral by the GP for specialist level care, most commonly to specialist diabetes outpatient clinics[6]. However, due to the increasing prevalence of the condition and the finite capacity of specialist outpatient clinics, new models of meeting community needs for complex diabetes management are required.

The Chronic Care Model (CCM) is a well known model of care for people with chronic conditions that suggests that optimal health outcomes are achieved when a prepared and proactive practice team interacts with informed and activated patients[7]. This model has informed policy and been adapted for use in different countries and different health care systems for caring for patients with various chronic conditions, including T2DM[8]. The model describes the six elements considered to be essential for improving the care of people with chronic disease. These elements include delivery system design, self management support, decision support, clinical information systems, community resources and health care organisations.

The Inala Chronic Disease Management Service (ICDMS) is a new model of T2DM care that is informed by the CCM with a particular focus on redesigning the health care delivery system and improving patients' self management skills - two of the six key elements of the CCM. The conceptualisation of the ICDMS was informed by the knowledge that there were unacceptably long waiting lists for patients to gain access to specialist diabetes outpatient clinics; the belief that with adequate training and support, primary care providers could provide high quality care for people with diabetes; and the desire to increase efficiency of care by making better use of the skills of providers. The aim of the intervention was to improve the efficiency and effectiveness of care with the flow on effects of potentially being more cost effective. This paper describes the ICDMS clinical model and the methods used to evaluate it, and provides baseline data from the participants. The discussion highlights the challenges faced, and the trade-offs between service delivery and experimental control in the context of this effectiveness trial.

### The ICDMS clinical model

The ICDMS operates from within a general practice that is co-located within the Inala Community Health Centre. Care is provided by a multidisciplinary team consisting of an endocrinologist, GP Clinical Fellows (GPs who have undertaken focussed post-graduate training in complex diabetes care), diabetes nurse educators, dietitian, podiatrist and psychologist. The ICDMS clinical model has three discrete components: the assessment and complications screening; the weekly multidisciplinary diabetes clinic; and the review and discharge phase. The ICDMS clinical model aims to enable each patient achieve target levels for blood glucose, lipids, and blood pressure (BP), or as close to target as realistic, and to then return to their referring GP as soon as practicable for their ongoing diabetes care. The key elements of the clinical model are presented in Figure 1.

**Figure 1 F1:**
[figure not shown]
**Flowchart describing study design for evaluating Inala Chronic Disease Management Service clinical model**.

### Comprehensive assessment and complications screening

At the patient's first visit to the ICDMS, a diabetes nurse educator completes a comprehensive assessment and complications screening. This assessment includes anthropometric data, self-reported current medications (prescription, over-the-counter medications, and complementary medicines), relevant diabetes history (year of diagnosis, family history of diabetes, previous gestational diabetes, frequency of hypoglycaemic episodes, day-to-day glycaemic control, and frequency of self monitoring of blood glucose levels), smoking status, alcohol consumption, current physical activity levels, weight management, and relevant medical history including known macro- and microvascular complications of diabetes. Retinopathy screening is conducted on site using a non-mydriatric camera with retinal photographs taken by a trained nurse and interpreted by a trained GP[9]. The patient's feet are screened, and any patients with acute foot complications or with a "high risk" foot are immediately referred to the ICDMS podiatrist for assessment. Results from existing pathology tests for glycated haemoglobin (HbA1c), serum lipids, folate, vitamin B12, creatinine, liver function tests, and urinary albumin:creatinine ratio are used if tested within the previous three months. If not, patients are provided with pathology request slips. An onsite, publicly funded, pathology collection point facilitates the timely processing of requests.

### Weekly multidisciplinary clinic

The ICDMS multidisciplinary clinic is conducted one morning per week and is serviced by all members of the team (endocrinologist, GP Clinical Fellows, diabetes nurse educators, dietitian, podiatrist, and psychologist). In consultation with the patient, the GP Clinical Fellow reviews the information gathered during the patient's assessment and complications screening, determines the patient's own goals for diabetes treatment, and develops a patient specific management plan to address the identified issues. The endocrinologist reviews the management plans and co-consults with the GP Clinical Fellow if the patient's clinical issues are particularly complex. Evidence-based guidelines or protocols inform management of hyperglycaemia[10,11], chronic kidney disease[12], hypertension[13], dyslipidemia[13,14], and macrovascular disease[13]. Referrals to an ophthalmologist are made if retinopathy or other sight threatening pathology is detected, as per Australian National Health and Medical Research Council (NHMRC) guidelines[15]. Referrals are also made to the allied health personnel for immediate assessment and follow-up as required.

To ensure timely and comprehensive communication between the ICDMS and the referring GP, a summary of the assessment and management plan is forwarded to the GP within one week of the patient attending the clinic. This summary also includes any specific recommendations for the GP to follow-up, and informs the GP if the patient has been discharged from the ICDMS. GPs are provided with a direct contact number at the ICDMS for queries, concerns and rapid re-assessment of patients.

### Review and discharge

Phase Three focuses on execution of the management plan developed at the clinic, with the aim of discharging the patient back to their referring GP as soon as targets have been reached and stabilised. Patients newly commenced on insulin, or those who need their insulin regimens revised to achieve optimal glycaemic control are enrolled into the ICDMS insulin stabilisation service (ISS). Patients on the ISS are contacted two or three times a week by a diabetes nurse educator to review their daily blood sugar levels (BSLs). Under supervision of a GP Clinical Fellow, the diabetes nurse educator makes small, incremental adjustments to the patient's insulin regimen to achieve stable and optimal BSLs. Patients are reviewed at the weekly clinic as required to monitor and adjust other treatments. Where appropriate, patients are strongly encouraged to attend either the self-management or weight loss programs provided by the ICDMS or other relevant programs provided by the Inala Community Health Centre.

## Methods/Design

### Study aim and design

The overarching aim of the ICDMS clinical model is to provide comprehensive and integrated clinical care for people with complex T2DM to achieve optimal glycaemic control. An open controlled intervention trial is comparing the impact of the ICDMS clinical model on patient outcomes compared to usual care provided to comparable patients attending the Princess Alexandra Hospital (PAH) Specialist Diabetes Outpatient Clinic. Figure 2 shows the study design. Usual care at the PAH involves assessment and review by a consultant endocrinologist or supervised training registrars or residents and referral to a diabetes nurse educator or other allied health personnel as required. Patients that have relatively stable control tend to not be discharged back to their referring GP, but continue to attend the clinic for annual reviews.

**Figure 2 F2:**
[figure not shown]
**Inala Chronic Disease Management Service clinical model of care**.

### Patient population and recruitment

The target population for the ICDMS evaluation study was patients with T2DM who had been referred by their GP to the PAH specialist diabetes outpatient clinic. Both new and existing patients of the specialist diabetes outpatient clinic who were at least 18 years old and able and willing to provide informed consent were eligible to participate. Interpreter services were available for patients who needed assistance with their English. Exclusion criteria included being on haemodialysis, renal transplant patients because of their need for frequent visits to the tertiary hospital, hypoglycaemic unawareness, or pregnancy.

Recruitment of patients to the ICDMS occurred between September 2007 and April 2008. The ICDMS focussed on patients who lived within the Queensland Health designated catchment area for the Inala Community Health Centre or attended a GP who practiced within this area who had been referred by their GP to the PAH specialist outpatient clinic. These patients were identified from the PAH specialist outpatient clinic's appointment booking system. Approval was sought from the patient's GP for the ICDMS to contact the patient by letter and/or phone to invite them to attend the ICDMS rather than the PAH specialist outpatient diabetes clinic. No GP refused consent for their patient to attend the ICDMS, and all patients invited to attend the ICDMS did so. All patients attending the ICDMS underwent the initial comprehensive assessment and complications screening described above, irrespective of previous attendances at the PAH.

One hundred and forty nine consecutive patients with T2DM attending the PAH specialist diabetes outpatients clinic from January to April 2008 were invited to participate in this study as the control group. Their recruitment occurred in the clinic whilst they waited for their appointment with the specialist. Only four patients refused to participate.

### Sample size and power calculation

A total of 240 patients (120 per group) were needed to detect a difference between study groups of 0.5% in the change in HbA1c from baseline, assuming a standard deviation of HbA1c (our primary outcome) of 1.4%, using a 2-sided test with a significance level of 0.05 and 80% power. We estimated a 20% discontinuation rate for the 12 month follow-up period, thus we aimed to enrol 300 patients (150 per group).

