### Outcome assessment

Data from patients were collected at baseline by reviewing medical records for clinical data and self-completed questionnaires for demographic data, including age, education level, ethnicity, duration of diabetes, and history of co-morbidities. Clinical data will be collected again at six and 12 months in similar fashions.

The ICDMS aimed to enable patients to achieve optimal glycaemic control and therefore, the primary outcome is HbA1c at 12 months. The proportion of patients with HbA1c ≤ 7% (ie. within the NHMRC guidelines for glycaemic control[15]; between 7.1% and ≤ 8%; between 8.1% and 10%; and greater than 10% will be calculated and compared between groups.

Secondary outcome measures include improvements in modifiable cardiovascular disease risk factors, and improvements in patient quality of life and diabetes self-efficacy. Improvements in modifiable cardiovascular disease risk factors include decreased total and low density lipoprotein (LDL) cholesterol and blood pressure (BP), increased levels of physical activity, and increased proportion of non-smoking participants. Additionally, the proportion of participants with BP and LDL cholesterol at target will be assessed at 12 months. Quality of care indicators included the proportion of patients with microalbuminuria on Angiotensin-Converting Enzyme (ACE) inhibitors or Angiotensin 2 Receptor Antagonists (A2RB); the proportion of patients with dyslipideamia on statins or fibrates (if indicated and tolerated); and the proportion of patients on prophylactic aspirin (as was accepted best practice at the commencement of this study).

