### Statistical analysis

Baseline characteristics that differ significantly between the two patient groups and the two groups of general practices will be identified using descriptive statistics and adjusted for in all multivariate analyses. Characteristics of participants who complete and withdraw will be compared. To ensure the generalisability of the results, the number of non-participants, their age and gender, and their reason for non-participation will be recorded.

Analyses of primary outcomes will be done on an intention to treat basis assuming return to baseline values for any patients who do not complete follow-up. Measures of the outcome value at baseline will be included in the regression analysis as a covariable. Other covariables may include any characteristics that are not balanced between the groups at baseline. A sensitivity analysis will investigate the effect of participant loss to follow-up on the intervention effect. Statistical significance will be based on two-tailed tests, with p < 0.05 considered significant.

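### The 80% power claim uses an HbA1c SD of 1.4%, while Table 1 shows 1.9% in both groups; the two agree only if the unstated baseline to 12-month correlation is about 0.7 or higher

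*Protocol article*

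**What the plan says.** All references are to the protocol article.

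- *Sample size and power calculation*: the study is sized at 120 evaluable patients in each arm, 240 in all, for a between-group difference of 0.5 percentage points in HbA1c change. The remaining assumptions are given as "assuming a standard deviation of HbA1c (our primary outcome) of 1.4%, using a 2-sided test with a significance level of 0.05 and 80% power". Allowing for one patient in five being lost over the year, the enrolment target is 150 in each arm, 300 in all.
- *Outcome assessment*: "the primary outcome is HbA1c at 12 months".
- *Statistical analysis*: the baseline value of the outcome enters the regression as a covariable. Baseline characteristics that differ significantly between groups are to be "adjusted for in all multivariate analyses". The next paragraph is softer and says only that other unbalanced characteristics may be included.
- *Baseline results*, Table 1: HbA1c mean (SD) is 7.9 (1.9) in usual care and 8.5 (1.9) in ICDMS. The footnotes give 1 and 16 missing values, so 144 and 169 are observed. The groups are 145 and 185. The text also reports imbalance in age, sex, blood pressure and neuropathy.

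**The concern.** The effect is on the change from baseline, the SD is described as that of HbA1c, the primary outcome is the 12-month level, and the planned model adjusts for baseline. These call for different SDs, and the paragraph does not say which one 1.4% is. Read as written, it is the SD of the level, and the article's own data contradict it.

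The calculation also treats the groups as if they were balanced. In this geographically controlled design, several covariates that the plan adjusts for predict group membership, which costs precision on the group effect.

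At stake is the interpretation of a null result. If the true power for 0.5% is well below 80%, a non-significant finding says less than the power statement suggests.

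**Working it through.** **Inputs from the article.** Difference 0.5; SD 1.4 (assumed) and 1.9 (observed); two-sided alpha 0.05; power 80%; 120 per group planned; 185/145 enrolled; 20% loss. The text gives a total of 335, but the two groups sum to 330; the group sizes are used here.

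**Not in the article.** The correlation ρ between baseline and 12-month HbA1c. It is an assumption, shown from 0.3 to 0.8.

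**1. The plan's own figure.**
n per group = 2 × (1.960 + 0.8416)² × 1.4² / 0.5² = 123.1.
Power at 120 per group = Φ(0.5 / (1.4 × √(2/120)) − 1.960) = 79%.
Dropout: 120 / 0.8 = 150.
The planned figures therefore reproduce, apart from a trivial rounding down.

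**2. Can sampling error explain 1.9 against 1.4?** With 144 and 169 values, the normal-theory 95% interval for the SD is about 1.70 to 2.15 in usual care and 1.72 to 2.13 in ICDMS. Neither includes 1.4.

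**3. SD 1.9 as labelled.**
n per group = 2 × (2.8016)² × 1.9² / 0.5² = 226.7, so 227.
Power at 120 per group = Φ(0.5 / (1.9 × 0.1291) − 1.960) = 53%.
Enrolment less 20%: 185 × 0.8 = 148 and 145 × 0.8 = 116; √(1/148 + 1/116) = 0.1240; power = Φ(0.5 / (1.9 × 0.1240) − 1.960) = 56%.

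**4. What correlation reconciles 1.4 with 1.9?**
As a baseline-adjusted residual SD, 1.9 × √(1 − ρ²) = 1.4 gives ρ = 0.68.
As an SD of change, 1.9 × √(2(1 − ρ)) = 1.4 gives ρ = 0.73.

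**5. Collinearity cost.** Standardised differences from Table 1: HbA1c 0.6/1.9 = 0.316; age 0.279; sex 0.389; systolic pressure 0.569; neuropathy 0.521. Their squares sum to 0.924. With group fractions 145/330 and 185/330 (product 0.246), and covariates taken as uncorrelated within groups:
variance inflation = 1 + 0.246 × 0.924 = 1.23.
Baseline HbA1c alone costs only 1.02, which the baseline-only columns below ignore. Adding diastolic pressure gives 1.28. Education is left out: the text calls it different, but Table 1 gives P = 0.51.

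**6. Power under the planned model.** Effective SD = 1.9 × √((1 − ρ²) × inflation).

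| Assumed ρ | 120/120, baseline only | 120/120, inflation 1.23 | 148/116, baseline only | 148/116, inflation 1.23 |
|---|---|---|---|---|
| 0.3 | 57.0% | 48.7% | 60.4% | 51.9% |
| 0.5 | 65.3% | 56.5% | 68.8% | 59.9% |
| 0.6 | 72.2% | 63.3% | 75.6% | 66.8% |
| 0.7 | 81.4% | 73.1% | 84.4% | 76.5% |
| 0.8 | 92.5% | 86.6% | 94.3% | 89.1% |

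At 120 per group, 80% power needs an effective SD of 0.5 / (2.8016 × 0.1291) = 1.38. That is ρ = 0.69 with baseline only and 0.75 with inflation 1.23. At 148/116 the SD may be 0.5 / (2.8016 × 0.1240) = 1.44, so ρ = 0.65 and 0.73.

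**7. If 1.4 really is the residual SD.** Inflation gives 1.4 × √1.23 = 1.55, and power at 120 per group falls from 79% to about 70%.

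**8. Detectable difference at 80% power, 148/116, inflation 1.23.** 2.8016 × 0.1240 × effective SD = 0.347 × 1.82 = 0.63% at ρ = 0.5; 0.347 × 1.50 = 0.52% at 0.7; 0.347 × 1.26 = 0.44% at 0.8.

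**The case against.** The strongest reply is that Table 1's 1.9% is a cross-sectional baseline SD, whereas the effect is on change and the model adjusts for baseline. At a high enough correlation, 1.4% is a reasonable residual or change SD. This stands, and it limits the conclusion: a reader might infer that the trial simply has 53% power, but that is the power of an unadjusted comparison of 12-month levels (or of change scores at ρ = 0.5), not of the planned analysis.

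A reader might also infer that covariate adjustment pushes the variance above 1.9². It does so only if ρ is below √(1 − 1/1.23), about 0.43; above that, the gain from baseline HbA1c outweighs the collinearity cost. For the same reason, the inflation should not be applied to the unadjusted 1.9. The 1.23 also credits no outcome variance explained by the other covariates, and the plan is not firm about including them all.

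The planned intention-to-treat analysis keeps non-completers at their baseline value, so 148/116 is not the planned analysis set. With the 169/144 patients who have a baseline HbA1c and SD 1.4, power is 88% before any collinearity cost. Returning patients to baseline would, however, dilute the difference and alter the SD, and neither is modelled here. Enrolment did exceed the 300 target in total.

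Finally, 120 against 123 or 124 per group is no error worth raising, and a source for 1.4% may lie in a fuller protocol. None of this removes the conflict in the published paragraph: it names 1.4% as the SD of HbA1c, and the same article reports 1.9%.

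**Conclusion.** The power statement is wrong as written and needs restating. Its SD, as labelled, conflicts with the trial's own data, and only an unstated correlation reconciles the two: about 0.7 or higher with baseline adjustment, about 0.75 once the imbalanced covariates are included (slightly lower at 148/116). For correlations from 0.5 to 0.8 with those covariates, power at 120 per group runs from about 57% to 87%. The documents do not show that 80% power is missed, only that it is not supported.

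This rests on 1.9% holding at 12 months, on covariates uncorrelated within groups, and on the assumed range of correlations. It is a fault in a planning assumption and its labelling, not in the sample size arithmetic.

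**What to change.** In *Sample size and power calculation*:

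- State whether 1.4% is the SD of the level, of the change or of the baseline-adjusted residual, and give its source.
- Restate power, or the difference detectable at 80% power, for the actual 185/145 enrolment under the planned adjusted model. Use the observed SD of 1.9%, a stated correlation with a range around it, the collinearity cost of the covariates that will be included, and the planned handling of non-completers.
- Say that a null result will be interpreted by its confidence interval, not by the design power.

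The cost is a rewritten paragraph and possibly a less favourable stated power. No extra patients and no change of design are needed.
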